**Fig. 1 Fig1:**
[figure not shown]
*Flowchart* for the rTMS study protocol. The participants will be selected and the eligibility assessment will be applied. They will then be randomized and allocated to group 1 (starting with rTMS-active) or group 2 (starting with rTMS-sham). Five sessions of rTMS-active and sham will be applied to participants in each group over one week, with a washout period (two weeks). Assessments will be before and after each intervention period (i.e. sham and active) using the motor and sensory scales, spasticity scale, and surface electromyography

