### Inclusion criteria

Participants will be included if they have agreed to participate in the study and have signed an informed consent form. They will have a clinical diagnosis of iSCI with non-progressive etiology which is characterized by spinal, vascular, and infectious trauma. Neuroimaging examinations, such as computed tomography and nuclear magnetic resonance imaging, will be used to exclude SCIs due to progressive worsening conditions such as neurodegenerative, tumor, and demyelinating pathologies [28, 29]. The participants should be at least six months post iSCI, clinically stable, aged 18–60 years, have a satisfactory score in Scale of Mini-Mental State Examination (MMSE) (i.e. cut-off points of 13 for illiterates, 18 for low and middle school, and 26 for high school), have no pathological alterations on electroencephalography (EEG), be clear of depression as assessed by the Hamilton Depression Scale (HAM-D), and be currently receiving conventional sensorimotor physiotherapy, to a maximum of three times per week.

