#### Data analysis

The analysis will follow a pre-specified analysis plan, based on comparing the groups as randomized (intention-to-treat). All data will be presented as mean ± standard deviation and summarized in frequency tables. We will use Microsoft Office Excel for Windows (version 2013) to store the data and the Statistical Package for Social Sciences (SPSS-IBM®) version 21 for Windows to perform statistical analysis. The normality and homogeneity of all variables (i.e. primary and secondary outcomes) will be tested with the Shapiro–Wilk and Levene’s test, respectively. For non-parametric data, the Friedman test will be used followed by the Wilcoxon post hoc test. We will use the ANOVA two-way (2 × 4) for the inferential statistic of the parametric data, with Tukey’s post hoc tests. Significance level will be set as α ≤ 0.05 and the effect size will be calculated by eta-squared (*ŋ*
^*2*^).

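### The non-parametric branch names Wilcoxon pairwise tests without an adjustment or a deciding contrast; run at 0.05, they do not hold the family-wise error once one assessment differs

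*Protocol article*

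**What the plan says.** All of the following is in the Protocol article. The Data analysis section chooses the branch by testing every primary and secondary outcome for normality and homogeneity; these "will be tested with the Shapiro–Wilk and Levene’s test, respectively". It then fixes one procedure per branch:

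- Parametric: "We will use the ANOVA two-way (2 × 4) for the inferential statistic of the parametric data, with Tukey’s post hoc tests".
- Non-parametric: "For non-parametric data, the Friedman test will be used followed by the Wilcoxon post hoc test".

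One significance level serves both branches: "Significance level will be set as α ≤ 0.05 and the effect size will be calculated by eta-squared". The section names no per-comparison level, says nothing on whether the Wilcoxon p-values are adjusted, and does not list the pairs to be compared. It refers to a plan outside the article: "The analysis will follow a pre-specified analysis plan, based on comparing the groups as randomized (intention-to-treat".

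The number of assessments comes from the Fig. 1 caption: "Assessments will be before and after each intervention period (i.e. sham and active". With two periods that makes four, which fits the second factor of the 2 × 4 ANOVA.

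**The concern.** Tukey's procedure controls the error over all pairwise comparisons by construction. A Wilcoxon signed-rank test compares two conditions and has no such control built in. The two branches therefore appear to set different error standards for the same comparisons, and a preliminary test on about 20 participants decides which applies.

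The non-parametric branch is likely to be used. The Modified Ashworth Scale is described with grades 0 to 4, the ASIA motor score sums muscle grades of 0 to 5, and the sensory score sums items of 0 to 2. The primary outcome could fall into this branch.

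The Friedman test acts as a gate, but it protects the family of pairs only when all four assessments are equal. Once one truly differs, the gate tends to open and the remaining equal pairs are each tested at 0.05. The branch also names no comparison of active with sham as the one that decides, so a reader could pick among up to six results.

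**Working it through.** **Inputs**

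- Level 0.05, Friedman then Wilcoxon, Tukey in the other branch only: Data analysis section.
- Four assessments: Fig. 1 caption.
- n = 14 and n = 20: Sample size section (14 required, 20 recruited).
- Assumed, not in the article: all six pairs are tested, no adjustment is made, within-person correlation is 0.7, and the scores are normal. These assumptions serve only to size the effect.

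The 0.05 is a chosen level, so there is no derived figure to reproduce. The sample-size calculation does not bear on this point.

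**Step 1: number of pairs.** 4 × 3 / 2 = 6.

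**Step 2: no gate.** Six independent tests at 0.05 would give 1 − 0.95^6 = 0.265. The pairs share data, so the simulated figure is lower, about 0.21. Neither figure describes this plan, because the Friedman test comes first.

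**Step 3: with the gate, no assessment differs.** Four equicorrelated assessments were simulated, with Friedman at 0.05 and then six signed-rank tests (4,000 trials per cell). The chance of at least one false rejection was 0.052 at n = 20 and 0.040 at n = 14. A separate set of 20,000 runs per scenario, with exact Wilcoxon tests, normal and exponential errors and n from 7 to 20, gave 0.035 to 0.044. Control is kept here.

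**Step 4: with the gate, one assessment differs.** Scores step up once after baseline and then stay flat. Three of the six pairs (2–3, 2–4, 3–4) are true nulls; with no help from the gate, three independent tests would give 1 − 0.95^3 = 0.143.

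| n | Step | Gated family-wise error | Holm over six pairs |
|---|---|---|---|
| 20 | 0.8 SD | 0.129 | 0.044 |
| 20 | 0.5 SD | 0.099 | 0.027 |
| 14 | 0.8 SD | 0.123 | 0.037 |
| 14 | 0.5 SD | 0.103 | 0.028 |

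The largest is 0.129 / 0.05 = 2.6 times the stated level. A further run of the same set-up put the range at about 0.09 to 0.13. The 20,000-run set, with a step so large that the gate almost always opens, gave 0.119 to 0.125 for one differing assessment, and 0.089 to 0.096 when the assessments form two equal pairs. Holm after the gate stayed at or below about 0.049 throughout.

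**Step 5: one pair alone.** In the Step 4 set-up with the 0.8 SD step, the pair before versus after the second period (3–4) was falsely rejected in 0.048 of trials at both sample sizes. That is nominal.

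**Step 6: columns arranged by treatment instead of calendar time.** The columns become before and after active, before and after sham, with half the participants in each sequence. With the same step, the true-null pairs are before active versus before sham, and after active versus after sham. The gated error over these two pairs was 0.028 to 0.040, below 0.05.

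**The case against.** The strongest reply is that the article never says the Wilcoxon tests are unadjusted, nor that all six pairs will be tested. It is a condensed account that cites an analysis plan, and adjustment of post hoc pairs is a detail often left there. That stands: a reader might infer that the plan is to test six pairs uncorrected, but the text only fails to name an adjustment.

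A reader might also infer that error control disappears whenever normality fails. Step 3 contradicts this, because the Friedman gate holds the error when nothing changes.

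Nor is a false before-versus-after-active difference itself more likely than 5%. Step 5 shows the single pair at its nominal rate. The calendar-time columns pool both sequences, so they contain no before/after-active pair at all, and Step 6 shows no inflation once the columns follow treatment.

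The one-step pattern can be questioned too. Participants must be clinically stable and already "be currently receiving conventional sensorimotor physiotherapy, to a maximum of three times per week", and the Dropout criteria section withdraws anyone who changes rehabilitation. Physiotherapy does not begin at baseline, so it gives little reason to expect a single jump, and steady gains would leave no equal pairs to reject falsely. The pattern is an illustration, not a forecast. However, the article hypothesises improvement, and its Study design section allows motor effects lasting up to two weeks, the length of the washout. Complete equality of the four assessments is therefore not the only case to guard against.

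What survives is that the article chose a post hoc method for both branches in adjacent sentences, and the one named here, at the only stated level, does not hold its family-wise error in general.

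**Conclusion.** The point holds in a limited form. The published text names family-wise control for the parametric branch only, and the non-parametric branch has neither a named adjustment nor a deciding active-versus-sham comparison. If the up to six calendar-time pairs are each tested at 0.05 after Friedman, the family-wise error is near 0.04 with no differing assessment and about 0.09 to 0.13 per outcome with one differing and three equal. This rests on assumed unadjusted testing of all pairs, correlation 0.7 and a step of 0.5 to 0.8 SD.

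The inflation belongs to the family, not to any one pair. The documents support neither a claim that error control is lost altogether nor one that the active-treatment comparison is individually biased towards significance. The defect is worth correcting because the branch probably applies to the ordinal outcomes and the correction is cheap.

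**What to change.** In the non-parametric branch, name one deciding contrast per outcome: each participant's change over the active period minus the change over the sham period, tested once at two-sided 0.05. This answers the crossover question directly and needs no adjustment across time points. Report any Wilcoxon time-point pairs as secondary, list them, and adjust them by Holm. If the analysis plan already specifies an adjustment, it is enough to state it in the article and add the deciding contrast.

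The cost is one sentence and somewhat less power for individual pairs. The pairs should be tested on all participants together. Within a sequence group of seven, the smallest exact two-sided Wilcoxon p-value is 2 / 2^7 = 0.0156, above the first Holm threshold of 0.05 / 6 = 0.0083, so no pair could be declared significant. At ten per group the minimum is 2 / 2^10 = 0.002, which removes that obstacle.

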### Statistical analysis

#### Sample size

The sample size was calculated using statistical software (GPower 3.1.5) [57] on the main outcome measure (i.e. the motor score). This calculation was based on data from one study with a group of SCI individuals that received high-frequency rTMS at a frequency of 5 Hz on the vertex, which related to an improvement in clinical measures of the motor score [24]. The power was 0.80; the alpha was 0.05, the effect size was 0.65 (Cohen’s *d*). The sample estimation indicated that 14 participants would be necessary (i.e. seven per group). With an adjustment to allow for a dropout rate, we will recruit 20 participants.

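### For outcomes that fail the normality test, the Friedman fallback has no sequence or period term and does not secure the active-versus-sham comparison that the plan promises

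*Protocol article*

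**What the plan says.** All references are to the protocol article; no separate analysis plan is shown.

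- Data analysis states the aim as an analysis "based on comparing the groups as randomized (intention-to-treat").
- The test is chosen by looking at the data: "The normality and homogeneity of all variables (i.e. primary and secondary outcomes) will be tested", by Shapiro–Wilk and Levene respectively.
- If the data pass: "We will use the ANOVA two-way (2 × 4) for the inferential statistic of the parametric data, with Tukey’s post hoc tests". The two factors are not named.
- If they fail: "For non-parametric data, the Friedman test will be used followed by the Wilcoxon post hoc test". The Friedman levels and the Wilcoxon pairs are not named.
- "Significance level will be set as α ≤ 0.05"; sidedness is not given.
- Study design and Fig. 1 describe two one-week blocks separated by a two-week washout, with assessments before and after each block.
- Table 1 defines the primary outcome as motor-score change over the four weeks from baseline. By then every participant has had both active and sham.
- Participants must "be currently receiving conventional sensorimotor physiotherapy, to a maximum of three times per week".

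**The concern.** In a two-period crossover, the evidence for a treatment effect is the within-participant difference between active and sham, compared across the two randomised orders so that anything common to a period cancels. The 2 × 4 ANOVA can carry this through its group-by-assessment interaction. Friedman cannot, because it ranks four columns within each participant and asks whether the columns differ. Sequence and period have no place in it.

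A data-dependent switch could therefore move an outcome, possibly the primary one, from a test that contains the randomised comparison to one that need not. The risk is that a general improvement over four weeks is reported as an effect of stimulation.

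**Working it through.** **1. Which reading of the four levels?** Two are possible.

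- *Time order:* assessments 1, 2, 3, 4. A 2 × 4 layout is naturally two sequence groups by four assessments; a layout by condition would more naturally be treatment (2) by before/after (2). The baseline-to-four-weeks outcome points the same way.
- *Condition order:* before active, after active, before sham, after sham, with the sequences pooled. The Abstract and the Fig. 1 legend describe assessments in terms of active and sham, so this cannot be excluded.

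Both were checked.

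**2. Inputs from the article.** 20 participants, 1:1, so 10 per sequence. Two one-week blocks and a two-week washout put the visits at about weeks 0, 1, 3 and 4. α = 0.05. Effect size from Sample size: "The power was 0.80; the alpha was 0.05, the effect size was 0.65" (Cohen's d). The article gives no figure for the operating characteristics of the fallback, so there is none to reproduce.

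**3. Assumptions.** Normal scores, within-person error SD 1, between-person SD 3, two-sided tests, and a linear drift common to both sequences. The article gives no drift, so totals of 0, 0.6, 1 and 1.5 within-person SD over four weeks are shown. The article does not say what d is standardised by. Here it is the active-minus-sham difference of two scores, whose SD is √(1² + 1²) = √2, so the treatment effect is 0.65 × √2 = 0.919. Several thousand trials were simulated per setting; simulation error is about one percentage point.

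**4. False-positive rate, no treatment effect, N = 20, visits at weeks 0/1/3/4.**

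| Test | No drift | 0.6 SD | 1 SD | 1.5 SD |
|---|---|---|---|---|
| Friedman, time order | 5% | 28% | 71% | 98% |
| Friedman, condition order | 5% | 6% | 7% | 9% |
| Wilcoxon, before vs after active | 5% | 7% | 11% | 19% |
| Wilcoxon, after active vs after sham | 5% | 4% | 3% | 1% |
| Rank-sum between sequences on period difference | 4% | 4% | 4% | 4% |

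**5. Power at d = 0.65, no drift.** Friedman in time order about 22%; Friedman in condition order about 70%; Wilcoxon after active versus after sham about 76%; rank-sum between sequences about 74%. With 1.5 SD of drift, the after-active versus after-sham Wilcoxon falls to about 55%, while the rank-sum stays at about 75%.

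**6. Why the rank-sum is unaffected.** Let τ be the active-minus-sham effect and π the period-1 minus period-2 effect. The end-of-period-1 minus end-of-period-2 difference is centred on π + τ in group 1 and π − τ in group 2. Comparing the groups gives (π + τ) − (π − τ) = 2τ, so π drops out.

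**7. When is the fallback reached?** The Modified Ashworth Scale is listed with five grades, 0 to 4. In 20 participants such heavily tied data will almost certainly fail Shapiro–Wilk at one assessment or another. The ASIA motor score sums 20 muscle grades of 0 to 5 (20 × 5 = 100, the stated 50 + 50). Such a sum can look normal; the article gives no distribution from which to say how often it would fail.

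**The case against.** The strongest reply is that the damaging figures belong to one reading. If the levels are the four conditions, treatment is part of the Friedman factor, after active versus after sham is an available Wilcoxon pair that does not inflate, and power is close to that of the proposed test. This stands: a reader might infer that the fallback contains no treatment contrast at all, or has little power throughout, and the text supports neither. What remains is that the article does not secure this reading. Even under it, a significant omnibus or before/after-active result does not show superiority to sham, and period effects are left in.

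The second reply is that drift is assumed. A reader might infer from the ongoing physiotherapy that change without a treatment effect is to be expected. The article does not go that far: participants are at least six months post-injury and clinically stable, intensive rehabilitation is excluded, and anyone who changes rehabilitation is withdrawn. Background does call spontaneous recovery potentially substantial, and each scale is given four times, so some drift is plausible. With none, the error rate is nominal.

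Third, a reader might infer that the fallback is the likeliest path for the primary outcome, or that the Wilcoxon tests are unadjusted before/after comparisons. The article states neither, and contrasts and multiplicity adjustment may be in the analysis plan it mentions. That does not answer the main point: the omnibus test is fixed here, and it has no sequence or period term.

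**Conclusion.** The concern holds in a limited form. For non-normal outcomes the article fixes a one-factor, within-participant analysis that does not deliver the comparison of randomised groups promised in the same section. How much harm follows depends on two things the article leaves open: the ordering of the levels and the size of any drift. On the time-ordered reading, which the layout favours, false-positive rates reach tens of percent under moderate assumed drift, and a real effect is mostly missed when there is no drift. On the condition reading the inflation is small, and the fault is one of interpretation and unremoved period effects. The fallback is near certain for the Ashworth grade, a secondary outcome, and possible but not shown to be likely for the primary motor score.

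**What to change.** Before any unblinded analysis, replace the normality-dependent choice with one fixed analysis per outcome.

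- Remove the Shapiro–Wilk/Levene trigger and the Friedman branch.
- *Summed scores, including the ASIA motor score:* a mixed model with treatment, period and sequence as fixed effects and participant as a random effect, fitted to the end-of-period scores and tested on the treatment term.
- *Ashworth grade (main analysis) and summed scores (sensitivity analysis):* each participant's end-of-period-1 minus end-of-period-2 difference, compared between the two sequences with a Wilcoxon rank-sum test and reported with a Hodges–Lehmann estimate and confidence interval. The shift between sequences estimates 2τ (step 6), so estimate and limits are halved.

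Neither analysis removes carryover, so both still rely on the two-week washout.

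Cost: analysis wording only, with no added visits, data or participants. Where the rank test is used on normal data without drift, power is about 74% against 79% for a paired t test with 20 participants at d = 0.65, a loss of a few points.

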### Primary outcomes

To evaluate the motor and sensory effects of the high-frequency rTMS in the lower-limb motor area on M1 (i.e. vertex, Cz) and check the possibility of generating motor gains in participants with iSCI, we will observe the change from baseline motor values provided by the ASIA score.

Only one researcher will be responsible for evaluating all of the participants through both the sensorimotor scales and electromyography (EMG). This researcher will be a physiotherapist who will also receive training to use the scales and EMG device. In addition, we will perform an evaluation of the intra-rater reliability of the instruments used in this study. Adverse events will be collected using a form for adverse events at each assessment point and any adverse event related to the intervention will be reported.

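### Pre-treatment motor scores are collected in both periods but the stated 2 × 4 ANOVA has no covariate, so precision may be lost, by an amount the protocol does not let us fix

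*Protocol article*

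**What the plan says.** The trial is a two-period crossover in which everyone receives active and sham stimulation. The Fig. 1 caption sets the measurement times: "Assessments will be before and after each intervention period (i.e. sham and active) using the motor and sensory scales". Each participant therefore has four motor scores, two of them pre-treatment. Under Primary outcomes, "we will observe the change from baseline motor values provided by the ASIA score".

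The Data analysis section gives one parametric method: "We will use the ANOVA two-way (2 × 4) for the inferential statistic of the parametric data, with Tukey’s post hoc tests". Non-parametric data go to a Friedman test followed by Wilcoxon tests. The two ANOVA factors are not named, and no baseline adjustment appears anywhere in the article. The section also refers to a pre-specified analysis plan, which is not shown.

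The Sample size section states: "The power was 0.80; the alpha was 0.05, the effect size was 0.65" (labelled Cohen's d). It arrives at 14 participants and recruits 20. It gives no standard deviation, no within-participant correlation, and no statement of which difference the 0.65 standardises.

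**The concern.** Four levels match four assessments, so the natural reading is that the two pre-treatment scores are levels of the response. There are then three ways to reach an active-versus-sham comparison:

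- **Contrast of pre-to-post changes, period by period.** Each period's baseline is subtracted with weight 1. The change-from-baseline wording leads here too, if baseline means the score before each period.
- **Pairwise comparison of the two post-treatment scores.** Baseline gets weight 0.
- **The overall 2 × 4 interaction.** This is a 3-df test that does not isolate the treatment contrast.

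None of them estimates how much weight the baseline deserves. In a crossover, stable differences between people already cancel, so subtracting each period's baseline can add measurement noise rather than remove it. Precision is at stake on the primary outcome, and on the other scores analysed the same way, in a trial of at most 20 people.

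**Working it through.** **1. The plan's own figure.** The inputs are power 0.80, alpha 0.05 and effect size 0.65, from the Sample size section. The stated result is 14.

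- Repeated-measures ANOVA, 2 groups × 4 measurements, within-between interaction, f = 0.65/2 = 0.325, assumed correlation 0.5: N = 16, with power 0.788 at N = 14.
- Between-groups test of the same layout, 0.65 entered as f, correlation 0.5: N = 14, power 0.806.
- Paired t test with standardised difference 0.65: 21 two-sided, 17 one-sided.

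The 14 is therefore compatible with a 2 × 4 layout and an unstated correlation. It does not show that 0.65 is the standardised active-minus-sham difference in change. That is an assumption in what follows.

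**2. Variance.** Let D_pre and D_post be a participant's period differences in pre- and post-treatment scores, each with variance V and correlation r (assumed; with equal variances r is also the slope).

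- Change-score contrast: Var(D_post − D_pre) = 2V(1 − r)
- Post-only contrast: V
- Baseline-adjusted contrast: V(1 − r²)
- Adjusted/change ratio: (1 − r²) / [2(1 − r)] = (1 + r)/2, which is 0.50 at r = 0, 0.75 at 0.5, 0.90 at 0.8 and 0.95 at 0.9

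**3. Power against change-score and post-only contrasts.** Two-sided alpha 0.05, no carryover, noncentral t. The effect is 0.65 × √[2V(1 − r)].

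- Change: noncentrality 0.65√N (2.91 at N = 20, 2.43 at N = 14), N − 2 df
- Post-only: 0.65√N × √[2(1 − r)], N − 2 df
- Adjusted: about 0.65√N × √[2/(1 + r)], N − 3 df, averaged over chance baseline imbalance

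| r | N = 20: change / post-only / adjusted | N = 14: change / post-only / adjusted |
|---|---|---|
| 0 | 78 / 97 / 96% | 61 / 88 / 85% |
| 0.3 | 78 / 90 / 91% | 61 / 75 / 75% |
| 0.5 | 78 / 78 / 87% | 61 / 61 / 69% |
| 0.7 | 78 / 57 / 82% | 61 / 41 / 63% |
| 0.9 | 78 / 23 / 78% | 61 / 17 / 59% |

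Simulation gives the same figures to within a point or two. The adjusted analysis stays within 4 points of the better alternative in every row, and neither alternative does that.

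**4. Power against the 2 × 4 interaction test** (20,000 simulated trials, same effect scale).

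| slope | N = 20: 2 × 4 / adjusted | N = 14: 2 × 4 / adjusted |
|---|---|---|
| 0 | 93 / 96% | 79 / 84% |
| 0.5 | 71 / 86% | 52 / 69% |
| 0.75 | 42 / 81% | 31 / 63% |
| 0.9 | 21 / 78% | 18 / 59% |

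Part of this gap comes from replacing a 3-df interaction with a 1-df contrast. At slope 0.9 the adjusted and change-score analyses have equal power at N = 20, so there the covariate itself contributes nothing.

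**5. Carryover.** Suppose half the active effect τ is still present at the second pre-treatment score (an assumption for illustration).

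- *It persists through period 2.* Active-first participants have a post-score difference of 0.5τ and sham-first participants τ, so post-only averages 0.75τ. The mean active-minus-sham baseline difference is −0.25τ. Adjusted: (0.75 + 0.25r)τ = 0.825τ at r = 0.3 and 0.875τ at r = 0.5. Change score: τ.
- *It fades by the last assessment.* Change score: (1.5τ + τ)/2 = 1.25τ. Adjusted: (1 + 0.25r)τ = 1.075τ at r = 0.3 and 1.125τ at r = 0.5.

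**The case against.** The strongest reply is that the protocol does not name a change-score t test. A reader might infer that the plan forces the baseline slope to 1, so that 78% v 96% measures its loss. The documents do not support that. The factors are undefined, Tukey comparisons include post-active against post-sham with weight 0, and at slope 0 the 2 × 4 test itself trails adjustment by only 3 points at N = 20. This stands, and the size must be given against each comparator.

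Carryover is the second objection. The Study design section puts motor effects at up to two weeks, which equals the washout. Full weight on the period baseline protects against carryover that persists, and adjustment does not. This also stands, though the ordering reverses if carryover fades, so it is a trade-off to declare rather than a reason to leave the model alone.

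Third, covariates may be set out in the analysis plan that is not shown. This carries less weight because the article itself fixes a model, and that model has no covariate. It is also true that the criticism does not apply in this form on the Friedman/Wilcoxon route, and that a linear covariate model does not automatically suit the Modified Ashworth Scale, an ordinal scale graded 0 to 4.

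**Conclusion.** The point holds as one of efficiency. The stated model does not estimate the weight of baselines that the trial already collects. A reader might infer a biased estimate or an invalid test; nothing here shows either, and without carryover all the contrasts considered target the same effect.

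The size cannot be fixed. It depends on r, which is not given, on 0.65 being on the change-difference scale, which is not stated, and on adequate washout. Under those assumptions, the gain over change scores at 20 completers runs from about 18 points at r = 0 through 8 at r = 0.5 and 4 at r = 0.7 to none at r = 0.9. At 14 completers it runs from about 24 points to a loss of 2 to 3. Against the 2 × 4 interaction the gain at 20 completers is 3 points at slope 0 and 15 at slope 0.5, partly from the change in degrees of freedom. This is a worthwhile improvement, between optional and recommended, and not an error that invalidates the trial.

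**What to change.** For the primary motor score, state a single 1-df active-versus-sham contrast on the post-treatment scores. Use treatment, period and sequence as fixed effects and participant as a random effect. Enter the period-specific pre-treatment score as a covariate, split into the participant mean and the within-participant deviation, and remove the pre-treatment scores from the response levels. Use the same form for the sensory and Fugl–Meyer scores. Choose the method for the Modified Ashworth Scale separately.

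Report the change-score contrast as a sensitivity analysis, and say that the two estimates respond differently to carryover. In the Sample size section, state which difference the 0.65 standardises and what correlation was assumed.

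The cost is a change of wording before unblinding and one or two residual degrees of freedom. No new data or visits are needed, and SPSS can fit the model. The real downside is attenuation if carryover persists, which is why the sensitivity analysis belongs in the plan.
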